### Setting

This study will take place in 10 sites/ambulance Communication Centres distributed in 5 Canadian provinces/regions. They are all associated with sophisticated high-performing paramedic services and receiving hospitals already providing OHCA outcomes data to the CanROC network. Together, these 10 ambulance Communication Centres provide services to an estimated population of 13,919,809 [range 107,406 – 4,800,000], see Table 1. They process more than 1,725,000 9–1-1 calls per year, approximately 8312 of which are for eligible non-traumatic OHCA for which resuscitation is attempted. These sites have also been selected because their ambulance telecommunicators have various training backgrounds, and utilize various types of systems/platforms. All the selected Communication Centres have been providing telecommunication-assisted CPR instructions since or before April, 2004. Our research group has a decade-long history of collaboration with most of these partners. They have all provided a letter in support of this proposed project.

**Table 1 Tab1:** Annual 9–1-1 call volume, with sudden cardiac death distribution, per study site catchment area

Province	Community	Catchment Population	9–1-1 calls/year	Eligible SCD cases/year
British Columbia	Entire Province	4,800,000	600,000	2800
Alberta	Edmonton	4,100,000	600,000	2400
	Calgary			
Ontario	Toronto	2,790,000	280,000	1650
	London	455,526	66,000	291
	Niagara	431,346	60,000	250
	Sudbury	161,531	14,000	134
	Thunder Bay	107,406	9000	102
Nova Scotia	Entire Province	1,000,000	84,000	585
PEI	Entire Province	146,000	12,000	100
	Total	13,991,809	1,725,000	8312

### Study population

All patients with prehospital cardiac arrest (absence of a detectable pulse, unresponsiveness, and apnea) meeting the following criteria will be enrolled:
Presumed cardiac origin;Occur in the catchment area of the participating Communication Centre and corresponding CanROC site;Where resuscitation is attempted by a bystander and/or the emergency responders.

Case definitions will follow the Utstein Style guidelines for reporting cardiac arrest data [35, 36]. The number of patients not in cardiac arrest, for which telecommunication-assisted CPR instructions were implemented by the 9–1-1 caller as a result of the telecommunicators’ intervention, will also be reported.

The following patients will be excluded:
Cardiac arrest witnessed by paramedics after their arrival (no opportunity for bystander intervention);Patients who are “obviously dead” as defined by the Ambulance Act (decomposition, rigor mortis, decapitation);Trauma victims, including hanging and burns;Patients with cardiac arrest clearly of other non-cardiac origin including drug overdose, carbon monoxide poisoning, drowning, exsanguination, electrocution, asphyxia, hypoxia related to respiratory disease, cerebrovascular accident and documented terminal illness.

### Ethical considerations

We will seek full Research Ethics Board (REB) approval. Informed consent will not be required because patients are neither being targeted by any experimental intervention nor having their identifiable personal information used for research. Patients will undergo therapy and procedures normally provided either inside or outside the hospital and will not be exposed to undue risk or discomfort. Telecommunication-assisted CPR instructions are provided using a protocol that will not be modified as part of the proposed study. Strict patient confidentiality and safeguarding of all study-related documents will be assured, and the trial is publicly registered.

A note on the safety of providing CPR instructions to rare victims not in cardiac arrest: Providing CPR instructions to a population seemingly in cardiac arrest (unconscious and not breathing, or not breathing normally) is a practice supported by the 2015 International Consensus Guidelines on CPR in that, when in doubt about the presence or absence of signs of life, it is recommended to err on the safe side and initiate CPR [37]. For various reasons, since telecommunication-CPR instructions do not always result in CPR being performed on the victim, we observed in our Ottawa pilot study that a very small number of victims erroneously believed to be in cardiac arrest (4.4%) received bystander CPR [7]. After careful review of de-identified in-hospital medical records for every such patient, our independent patient-safety expert panel concluded that no physical injury could be attributed to the provided CPR. Although rib fractures and sternal fractures have been observed in as many as 30 and 15% of cardiac arrest victims during autopsy [38–41], another group from Seattle also failed to observe any adverse event resulting from CPR provided to patients not in cardiac arrest [42].

### Case identification

A list of potential eligible cases will first be identified by each ambulance Communication Centre for each month of the study period. The calls will be flagged using a combination of procedure and complaint codes for inclusivity. Dispatch platform systems differ between sites, thus, details will be outlined with each Communication Centre to ensure flagging of cases is consistent. The list will be sent to the Study Coordinating Centre in Ottawa for review.

The Coordinating Centre will cross-check each list against the CanROC list of confirmed and eligible cases for that site over the same time period. Cases will be matched using only run number and date and time of call to establish eligibility. The inclusion and exclusion criteria will be applied based on CanROC details to arrive at a monthly list of eligible cases from which data will be extracted.

### Classification of calls

After comparing the ambulance Communication Centre and CanROC lists, each cardiac arrest case will be classified into one of the following groups:
**Confirmed, eligible:** Cases that appear on both the Communication Centre list and the CanROC list and meet the study eligibility criteria. Further data will be collected from the 9–1-1 recording and the CanROC Registry.**Confirmed, ineligible:** Cases that appear on both lists, but do not meet all study eligibility criteria. No further data will be collected from these cases.**Missed:** Cases in the CanROC registry that meet the study eligibility criteria but were not flagged by the Communication Centre. The Communication Centre will be contacted to pull these cases, and further data will be collected from the 9–1-1 recordings and the CanROC Registry.**Overcalls:** Cases that are flagged by the Communication Centre as possible OHCA cases but do not appear in the CanROC Registry. We will collect further information from the Communication Centre for these calls.

### Sources of information

Each eligible, missed or overcalled case will be reviewed in detail using a variety of sources:
**Communication Centre:** Pre-specified quality assurance reports generated by the dispatch software in use as well as the 9–1-1 audio recordings will be available for the eligible, missed and overcalled cases. These sources will be reviewed to obtain information on key time intervals, caller/bystander characteristics, presence of agonal breathing, and details on telecommunication-assisted CPR.**CanROC Registry:** Each eligible and missed case will be linked to the CanROC Registry by run number and call date to locate standardized data that are being collected by the corresponding CanROC Sites. The CanROC minimal data set includes inputs from a variety of sources including: paramedic (ambulance) call reports, defibrillator files, fire medical assist reports, dispatch times and receiving hospital records.

### Method of assessment and data collection

#### Objective 1 (primary outcome)

Overall survival rate to hospital discharge: will be assessed via hospital medical records or via the coroner’s office among study-eligible patients. The CanROC Study group has been using this strategy successfully for more than a decade.

#### Objective 2 (and following secondary outcomes)

Overall community bystander CPR rate: “Bystander” CPR is performed by a person who is not part of an organized emergency medical system. Physicians, nurses, and paramedics may be described as performing bystander CPR if they are not part of the emergency response system involved in the victim’s resuscitation, but bystander usually refers to the untrained lay public [35]. “CPR” is an attempt to restore spontaneous circulation by performing chest compressions with or without ventilations.

The presence or absence of ongoing bystander CPR will be assessed by the first member of the emergency response team to arrive at scene, and is routinely documented on their patient care record.

#### Objective 3

Successful completion rate of telecommunication-assisted CPR instructions: is defined as CPR instructions provided by an ambulance telecommunicator to a 9–1-1 caller reporting a cardiac arrest victim, resulting in the administration of chest compressions to that victim by a bystander before EMS arrival. The recordings of all eligible OHCA calls from participating Communication Centres will be reviewed using an existing, standardized, and piloted data collection tool to collect information on variables pertaining to the successful delivery of telecommunication-assisted CPR instructions.Count of CPR instructions leading to chest compressions in rare victims not in cardiac arrest: As mentioned previously, providing CPR instructions to a population seemingly in cardiac arrest (unconscious and not breathing, or not breathing normally) is a practice supported by the 2015 International Consensus Guidelines on CPR [37]. After careful review of de-identified in-hospital medical records for every such patient, our independent patient-safety expert panel concluded that no physical injury could be attributed to the provided CPR [7]. For this reason, we do not plan (nor will we have the resources) to repeat the extensive in-hospital evaluation of such cases in this large, pragmatic, multi-centre study. Nonetheless, we plan to use the same standardized-piloted data collection tool as above to report the frequency with which CPR instructions led to chest compressions in rare victims not in cardiac arrest.

#### Objective 4

Agonal breathing: Can be defined as abnormal breathing, gurgling sound, moaning, or otherwise. Ambulance telecommunicators are required by protocol to inquire about the presence or absence of agonal or abnormal breathing. The standardized-piloted data collection tool will be used to independently document the presence or absence of agonal breathing, as described by the 9–1-1 caller to the telecommunicator. In a previous evaluation of inter-rater reliability for the recognition of agonal breathing, we observed substantial agreement (kappa statistics reported) for the presence of agonal breathing between telecommunicators and investigators, between telecommunicators, and within themselves when asked to repeat the exercise 4 months later [8].Recognition of OHCA by telecommunicators: According to protocols, ambulance telecommunicators assume the presence of cardiac arrest when the 9–1-1 caller describes a victim that is lifeless (unresponsive, not breathing, or not breathing normally).Recordings of the OHCA cases from participating ambulance Communication Centres will be reviewed and reasons why cardiac arrest may not have been recognized by the telecommunicator (including the presence of agonal breathing) will be documented.Determination of cardiac origin of OHCA: We will use the Utstein definition for cardiac arrest of cardiac origin [35]: “If an EMS provider or physician did not witness the cardiac arrest, he/she may be uncertain as to whether a cardiac arrest actually occurred. An arrest is presumed to be of cardiac etiology unless it is known or likely to have been caused by trauma, submersion, drug overdose, asphyxia, exsanguination, or any other non-cardiac cause as best determined by rescuers.”

Cardiac origin of OHCA is usually first suspected/documented by the paramedic crew responding to the scene, and subsequently confirmed using hospital discharge summaries or coroner’s data. This information will be readily available from the CanROC registry.

#### Objective 5

Speed with which OHCA is recognized and telecommunication-assisted CPR instructions are initiated: All 9–1-1 communications are recorded on digital files (for e.g. Canadian Voice Data Switching (CVDS) files) which include a running digital clock. We will record the time at which OHCA was recognized by telecommunicators, the time at which CPR instructions are initiated, and calculate time intervals from the initiation of the 9–1-1 call to these time stamps.

#### Objectives 6, 7, and 8

We are planning pre-determined subgroup analyses to study the impact of: 6) the studied community/site; 7) the telecommunication system/platform used; and 8) the telecommunicators’ training background and current local training on agonal breathing on the previously stated primary and secondary outcomes (Objectives 1–5).

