To obtain pooled estimates across all five regions, two methods will be used: First, we will use a random effects meta-analytical approach to pool the five region-specific intervention effect estimates and their standard errors. Next, we will use generalized linear mixed effects regression of the site-specific data with random intercepts for the sites and random slopes for time. All analyses will be conducted using SAS version 9.4 (SAS Institute, Inc., Cary, North Carolina).

#### Successful completion of telecommunication-assisted CPR instructions and frequency of CPR instructions leading to chest compressions in rare victims not in cardiac arrest – objective 3

We will use descriptive statistics with 95% CIs to describe successes in various stages of the implementation of CPR instructions (e.g. instructions offered, provided, completed, chest compressions initiated), and the frequency with which chest compressions are (rarely) going to be provided to a victim not in cardiac arrest.

#### Frequency and impact of agonal breathing on OHCA recognition by telecommunicators – objective 4

The frequency and impact of agonal breathing (proportion of missed OHCA as a result of agonal breathing) will be reported using kappa and descriptive statistics with 95% CI. Sensitivity, specificity, negative and positive predictive values will be computed with 95% CIs for the ability of ambulance telecommunicators to recognize OHCA over the telephone. OHCA recognition rates will be compared in the before and after periods using statistical analyses described above for Objectives 1 and 2.

#### Speed with which OHCA is recognized and telecommunication-assisted CPR instructions are initiated – objective 5

Descriptive statistics with 95% CIs will be used to describe various time delays occurring during telecommunication-assisted CPR instructions (e.g. time to OHCA recognition, to initiation, and to completion of instructions). We will compare these time intervals (continuous variable) in the before and after periods using statistical analyses similar to those described above for Objectives 1 and 2.

#### Objectives 6, 7, and 8

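### Recognition rates and times for Objectives 4 and 5 include arrests that began during or after the 9-1-1 call, and no analysis separates them

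*Protocol article*

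**What the plan says.** All references are to the protocol article.

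- **Study population.** Patients qualify "Where resuscitation is attempted by a bystander and/or the emergency responders". The only exclusion that depends on when the arrest happened is "Cardiac arrest witnessed by paramedics after their arrival (no opportunity for bystander intervention". Nothing requires the arrest to precede or coincide with the call.
- **Method of assessment, Objective 5.** The times of recognition and of first CPR instructions are read from the recording, and the study will "calculate time intervals from the initiation of the 9–1-1 call to these time stamps". The same origin applies to every case.
- **Data analysis, Objective 4.** "Sensitivity, specificity, negative and positive predictive values will be computed with 95% CIs for the ability of ambulance telecommunicators to recognize OHCA over the telephone". The share of missed arrests attributable to agonal breathing is also reported, and "OHCA recognition rates will be compared in the before and after periods using statistical analyses described above for Objectives 1 and 2".
- **Data analysis, Objective 5.** "We will compare these time intervals (continuous variable) in the before and after periods using statistical analyses similar to those described above".
- **Method of assessment, Objective 4.** Reviewers record why an arrest was not recognised. No analysis is tied to those reasons.

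**The concern.** Objectives 4 and 5 ask whether training on agonal breathing makes telecommunicators better and faster at recognising an arrest. Two groups of eligible patients do not fit that question as measured.

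The first group collapses during the call and is then recognised. They are true positives, but their interval starts before there was anything to recognise.

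The second group collapses after the call ends and before paramedics arrive. They have no recognition time, and no telecommunicator could have recognised them. Left in the denominators, they lower the recognition rate and the sensitivity, and they lower the apparent share of misses due to agonal breathing. Training cannot change their result, so they shrink the before-after difference that the hypothesis puts at 10 points or more.

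The plan drops paramedic-witnessed arrests because there was no opportunity for a bystander to act. A similar argument about opportunity applies to telephone recognition of an arrest that follows the call, but the plan does not carry it over to the recognition measures.

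**Working it through.** The article states no figure that depends on this point, so there is nothing to reproduce. The size is illustrated.

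**Inputs from the article**
- Recognition in the earlier multi-centre study (Prior related work): 65.9% of all OHCA, so 100 − 65.9 = 34.1% unrecognised.
- Share of those misses due to agonal breathing, same study: 47.6%.
- Hypothesised gain in recognition: at least 10 points.

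**Assumed, not in the article**
- x, the share of eligible arrests that begin after the call ends, none of them recognised: 2%, 5% or 10%.
- y, the share of recognised calls in which collapse comes d seconds after call start: y = 2–10%, d = 60–240 s.

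**Formulas**
- Recognition among recognisable arrests = 0.659/(1 − x).
- Post-call arrests as a share of all unrecognised arrests = x/0.341.
- Observed gain = 10 × (1 − x).
- Agonal share of misses without post-call arrests = 0.476/(1 − x/0.341), if post-call arrests all fall among the non-agonal misses.

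| x | Recognition among recognisable | Share of unrecognised that are post-call | True 10 points shows as | Agonal share of misses |
|---|---|---|---|---|
| 2% | 0.659/0.98 = 67.2% | 0.02/0.341 = 6% | 9.8 | 51% |
| 5% | 0.659/0.95 = 69.4% | 0.05/0.341 = 15% | 9.5 | 56% |
| 10% | 0.659/0.90 = 73.2% | 0.10/0.341 = 29% | 9.0 | 67% |

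**Ceiling on x.** Non-agonal misses were 0.341 × (1 − 0.476) = 17.9% of all OHCA in that study. If post-call arrests fall there, x cannot exceed 17.9%, and x = 10% would already make them 0.10/0.179 = 56% of non-agonal misses. The upper end of the range is therefore generous.

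**Times.** Mean recognition time rises by y × d: from 0.02 × 60 = 1.2 s to 0.10 × 240 = 24 s. If y and d are the same before and after, this shift is in both periods and cancels from the difference in means; the reported level stays too high.

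**Drift.** With x = 5% at baseline, a change of 1 to 3 points in x moves the all-case rate by 0.01 × 0.659/0.95 = 0.7 to 0.03 × 0.659/0.95 = 2.1 points. The article gives no reason to expect such a change at implementation.

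**The case against.** The strongest reply has four parts.

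**The Missed class is not a verdict on recognition.** Under Classification of calls it covers "Cases in the CanROC registry that meet the study eligibility criteria but were not flagged by the Communication Centre". It comes from matching two lists, so that the centre can be asked to retrieve the recording. A reader might infer that every such case becomes a false negative. The article does not say so: recognition is judged from the recording, and the sensitivity denominator is not spelled out. This part stands. The concern rests on eligibility, time origin and the absence of any exclusion, not on the Missed label.

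**The size is unknown and the damage limited.** A reader might infer that the same patients count both as misses and as slow recognitions, or that a programme effect could be manufactured. Neither is supported. The two effects fall on different patients, and a stable share only dilutes. Survival and bystander CPR do not use these definitions. This stands too.

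**All-case measurement from call start has merits.** Call initiation is an objective time stamp, and an all-case denominator matches the 65.9% benchmark. The first mention of abnormal breathing depends partly on when the telecommunicator asks, which training may change. Reviewers could also relabel agonal misses, the programme's target, as patients not yet in arrest. This is a sound argument against replacing the clock or the denominator outright. It is no argument against a parallel analysis.

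**The data collection tool is not shown.** It may already capture collapse timing, and the recorded reasons for non-recognition might reveal it. That would make the repair cheaper, but the article's stated analyses still make no use of it.

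**Conclusion.** The point holds for Objectives 4 and 5 only. As written, pre-arrest time counts as recognition delay for patients who collapse mid-call, and arrests that followed the call are not removed from the recognition measures. That they lower the sensitivity is an inference from the eligibility rule and the stated analyses, because the denominator is not set out.

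On an assumed share of 2–10%, the before-after contrast loses 0.2 to 1.0 of a true 10 points, which is modest. The descriptive results are more exposed: recognition would be understated by 1.3 to 7.3 points (67.2 − 65.9 and 73.2 − 65.9), and the agonal share of misses would be 51–67% rather than 47.6%. All these figures assume that no post-call arrest is recognised; the agonal figures also assume that all of them are non-agonal misses. The change is worth making because it is cheap and lets these objectives measure what training can alter.

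**What to change.** During the recording review already planned, code each eligible or missed case as: in arrest at call start; arrested during the call; arrested after the call ended; or uncertain. Any patient described as unresponsive or breathing abnormally during the call counts as in arrest during the call, never as a post-call arrest, so that agonal misses are not relabelled.

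Keep the all-case measures from call initiation for comparability. Pre-specify alongside them:

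- (a) the recognition rate, the sensitivity and the agonal share of misses, excluding arrests after the call ended (uncertain cases stay in);
- (b) recognition and instruction times restricted to patients in arrest at call start, with during-call arrests reported separately.

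No patient leaves Objectives 1 or 2. The cost is at most one field on the data collection tool and a few sentences in the plan, some judgement about collapse time, and a slightly smaller denominator in the parallel analysis.

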#### Objective 9 (not to be reported as part of project #1 per se)

Collect de-identified high-quality recordings for use in proposed Project#2: All 9–1-1 communications are recorded on digital files (for e.g. Canadian Voice Data Switching (CVDS) files), and are kept for a period of 5 years by ambulance Communication Centres. We intend to archive de-identified copies of this material for a period of 10 years, as required by standard operative procedures.

